## Abstract

**Background:**

Bile acid malabsorption (BAM) is one possible explanation for chronic diarrhea. BAM may be idiopathic, or result from ileal resection or inflammation including Crohn’s disease, or may be secondary to other conditions, including cholecystectomy, peptic ulcer surgery, and chronic pancreatitis. No “gold standard” exists for clinical diagnosis of BAM, but response to treatment with a bile acid sequestrant (BAS) is often accepted as confirmation. The SeHCAT (tauroselcholic [selenium-75] acid) test uses a radiolabeled synthetic bile acid and provides a diagnostic test for BAM, but its performance against “trial of treatment” is unknown. Fibroblast growth factor 19 (FGF-19) and 7-alpha-hydroxy-4-cholesten-3-one (C4) also offer potential new biomarkers of BAM.

**Objective:**

This protocol describes a multicenter prospective study to evaluate the diagnostic accuracy of SeHCAT and 2 biomarkers in predicting BAM as assessed by trial of treatment.

**Methods:**

Participating gastroenterology centers should have a minimum workload of 30 SeHCAT patients per annum. Patients should not be pregnant, on medication that could confound follow-up, or have any severe comorbidity. All eligible patients attending a gastrointestinal appointment will be invited to participate. On attending the SeHCAT test, blood and fecal samples will be collected for analysis of FGF-19 by enzyme-linked immunosorbent assay and for C4 and fractionated bile acids by liquid chromatography–mass spectrometry. A capsule containing radiolabeled SeHCAT will be administered orally and a scan performed to measure SeHCAT activity. Patients will return on day 7 to undergo a second scan to measure percentage SeHCAT retention. The test result will be concealed from clinicians and patients. BAS will be dispensed to all patients, with a follow-up gastroenterologist appointment at 2 weeks for clinical assessment of treatment response and adherence. Patients responding positively will continue treatment for a further 2 weeks and all patients will have a final follow-up at 8 weeks. The diagnostic accuracy of the SeHCAT test and biomarkers will be analyzed at different thresholds using sensitivity, specificity, positive and negative predictive value, likelihood ratios, and area under the curve in a sample of 600 patients. Multivariable logistic regression models will be used to assess the association between presence of BAM and continuous SeHCAT retention levels after adjustment for confounders.

**Results:**

Funding is being sought to conduct this research.

**Conclusions:**

The SeHCAT test for diagnosis of BAM has been in common use in the United Kingdom for more than 30 years and an evidence-based assessment of its accuracy is overdue. The proposed study has some challenges. Some forms of BAS treatment are unpleasant due to the texture and taste of the resin powder, which may negatively affect recruitment and treatment adherence. Trial of treatment is not as “golden” a standard as would be ideal, and itself warrants further study.

## Introduction

Chronic diarrhea is a common problem and the investigation and management of the condition places a significant burden on health services as well as on affected patients. The suggestion that bile acid malabsorption (BAM) can cause diarrhea was first described by Hofmann in 1967 [1]; since then, BAM has been identified as a possible explanation for persistent chronic diarrhea.

Bile acids are produced in the liver, stored in the gallbladder, and released upon eating for the digestion of dietary fat. They are then largely reabsorbed by the terminal ileum and returned to the liver, a process known as enterohepatic circulation. When the reabsorption process is disrupted, excess levels of bile acids enter the colon where they lead to increased motility and water secretion, resulting in diarrhea.

Evidence is accumulating that BAM is more common than was previously thought [2,3]; however, robust data on the prevalence of BAM do not exist. Three types of BAM have been defined. In BAM Type 1, the bile acid malabsorption results from ileal resection, ileal disease including Crohn’s disease, or bypass of the terminal ileum. BAM Type 2 relates to primary, idiopathic malabsorption, whereas BAM Type 3 represents malabsorption secondary to other conditions, including cholecystectomy, peptic ulcer surgery, chronic pancreatitis, and celiac disease.

A diagnostic test for BAM is provided by SeHCAT (tauroselcholic [selenium-75] acid), a radiolabeled synthetic bile acid. The SeHCAT test is a measure of the retention of radioactivity in the patient following administration of a capsule containing SeHCAT. The patient is scanned with a gamma camera 1 to 3 hours after taking the capsule and the scanning is repeated after 7 days to measure the percentage retention of the radiolabeled bile acid. A low SeHCAT retention level at day 7 represents an abnormal result for the test, indicating a positive diagnosis of BAM.

The SeHCAT test was introduced in the late 1970s; however, despite being used for more than 30 years, much of the available evidence is anecdotal knowledge built up over time rather than through systematic research. A recent survey on the use of SeHCAT in the United Kingdom provided an insight into the frequency of use of the test and the practicalities of its implementation in UK hospitals [4]. The study identified 73 centers using SeHCAT with a wide variation in the annual patient workload ranging from 1 to 300 tests (mean 51; median 30). An increase in referrals since 2010 was reported in response to demand from clinicians. Considerable variability in practical implementation of the technique was found, alongside a wide variation in the “normal” range of the SeHCAT percentage retention levels used for reporting, diagnosis, and treatment. The different approaches to definition of an abnormal result included a single threshold value (of which <15% retention was the most common), division into 3 categories (normal, borderline, and abnormal), or into 4 categories (normal, mild, moderate, and severe).

Patients with a diagnosis of BAM from a positive SeHCAT test may be offered treatment with bile acid sequestrants (BAS), such as cholestyramine, colestipol, and colesevelam. In general, patients who adhere to BAS treatment respond well and rapidly (within days) with significant reduction in bowel frequency and improvements in their quality of life [3]. However, certain BAS treatments are unpleasant to the patient and clear communication between the clinician and the patient is needed to highlight the expected benefits of treatment to ensure good adherence. Studies have found a relationship between SeHCAT retention levels and response to BAS treatment, with lower retention levels associated with greater resolution of symptoms [5].

A prospective survey was conducted in 2014 by the King’s Technology Evaluation Centre (KiTEC) to characterize the clinical indications for referring patients for a SeHCAT test across 38 UK centers and to describe the range of test results and treatment pathways [6]. Patients with BAM Type 1 represented 14% of more than 700 patients tested with the remainder split fairly equally between BAM Types 2 and 3. Using center-defined thresholds, 51% of results were defined as abnormal or borderline; however, only 37% of patients were prescribed treatment with BAS. Median SeHCAT retention levels were much lower for BAM Type 1 (2%) compared with BAM Types 2 and 3 (18% and 17%, respectively).

The diagnostic performance of the SeHCAT test across the range of thresholds in current use is poorly understood. There is no established “gold standard” for the diagnosis of BAM. However, diagnosis is sometimes made through a trial of treatment with BAS and response to treatment with BAS offers a potential reference standard, if taken by *all* patients, not just those who the SeHCAT test suggests may be in the abnormal range. A review by Riemsma et al [7] identified 3 studies which had taken this approach; however, the numbers were small (ranging from 13 to 46 patients) resulting in wide confidence intervals [7-10]. Specificity was more than 0.9 in all 3 studies; in the 2 studies that used a cut-off of 8% retention, sensitivity ranged from 0.67 to 0.95. Further research using larger samples is needed to assess the accuracy of the SeHCAT test in diagnosing the BAM condition as determined by response to BAS treatment.

In addition, 2 biomarkers have shown promising results as possible predictors of BAM, namely fibroblast growth factor 19 (FGF-19) and 7-alpha-hydroxy-4-cholesten-3-one (C4) [11,12]. Exploration of the performance of these biomarkers as alternative tools for discriminating between diagnoses could potentially improve diagnostic accuracy.

This protocol describes a study that will assess the diagnostic performance of the SeHCAT test and of 2 biomarkers in the prediction of BAM using a positive response to treatment with BAS as a definitive indication of the BAM condition. Improved diagnostic accuracy for BAM should, in turn, allow treatment of this debilitating condition to be optimized.

### Objectives

The primary research objective is to investigate the diagnostic accuracy of the SeHCAT test in providing a positive indication of BAM among people with chronic diarrhea who are clinically suspected of having BAM, using trial of treatment with BAS as the gold standard.

The secondary research objectives are to investigate:

The continuum of results of the SeHCAT test, overall and for different clinical populations;The feasibility of using the SeHCAT test to provide an indication of the severity of BAM (eg, mild, moderate, or severe);Adherence to treatment with BAS, overall and for different clinical populations;The diagnostic accuracy of 2 biomarker tests (FGF-19 and C4) in predicting BAM; andWhether the biomarkers can provide information on the nature of BAM.

The tertiary research objective is, for established cut-off values, to compare the sensitivity and specificity of the SeHCAT test with those of the 2 biomarkers in providing a positive indication of BAM using trial of treatment with BAS as the gold standard.

The research objectives can be translated into the following research questions:

Is SeHCAT an accurate test to provide a positive indication of BAM and what are the optimal cut-off thresholds?Can different cut-off thresholds be established for the different clinical populations under study?How do the cut-off thresholds currently in use for SeHCAT in UK centers compare with these optimal values?Is SeHCAT an accurate test to grade the severity of BAM?Does adherence to treatment with BAS differ for the different clinical populations studied?Can biomarkers provide an accurate test for a positive indication of BAM?Is the accuracy of biomarkers higher than that of SeHCAT in giving a positive indication of BAM?

## Methods

### Type of Study

The protocol describes a multicenter prospective study. Patients referred for suspected BAM will undergo a SeHCAT test and be tested for the biomarkers before undergoing treatment with BAS. Response to BAS treatment will provide a gold standard indication of a diagnosis of BAM. The diagnostic accuracy of the SeHCAT test and of the biomarkers will be assessed for the prediction of BAM.

### Setting

For a UK study, participating centers may be identified from the pool of 38 centers that took part in the recent KiTEC survey.

The proposed selection criteria for the centers are (1) a minimum workload of 30 SeHCAT patients per annum for the most recent calendar year for which data are available; (2) agreement to adopt a standardized SeHCAT test procedure; (3) laboratory capacity to collect, prepare, and deliver biological samples (blood and feces) for analysis at a remote site; and (4) formal commitment of a consultant gastroenterologist to participate in the study.

### Study Population

Participants in the study will be adults recruited from a population of patients attending a secondary care gastroenterology appointment, presenting with chronic diarrhea of unknown cause, in whom BAM is considered clinically possible. Patients will be included if they are suspected of having BAM Type 1 (following ileal resection, ileal disease including Crohn’s disease, or bypass of the terminal ileum), BAM Type 2 (primary idiopathic malabsorption), or BAM Type 3 (secondary to other conditions, including cholecystectomy, peptic ulcer surgery, chronic pancreatitis, and celiac disease). Potential participants will be screened for eligibility using a structured questionnaire and detailed clinical assessment.

### Exclusion Criteria

Potential participants may not enter the study if ANY of the following apply:

They are unable to provide informed consent;They are on medication that could confound follow-up assessment;They are pregnant or they are at risk of pregnancy and do not wish to take adequate precautions against pregnancy for the duration of the study;They have any severe comorbidity condition with less than 12 months life expectancy;They are unable or unwilling to undergo a SeHCAT procedure following the standard protocol and/or to provide blood and fecal samples; orThey are unwilling to undergo a course of treatment with BAS.

### Study Procedure and Outcome Measures

A diagram illustrating the study procedure is shown in Figure 1. All patients attending a gastrointestinal appointment at a participating center and fulfilling the inclusion criteria will be invited to participate in the study. Individual patient consent will be requested at entry by the recruiting clinician. All patients who fulfill the inclusion criteria will be given detailed information both verbally and in the form of a patient information sheet. During the gastrointestinal appointment, patients will be referred by the clinicians for a SeHCAT test. The patients will be given detailed information of all relevant pretest and posttest dietary and medication requirements.

When the patient visits the hospital for the SeHCAT test, blood and fecal samples will be collected before the test using standard clinical procedures. The samples will be transferred to the local biochemistry laboratory at each participating site, where they will be handled by a trained biomedical scientist and prepared for transfer to the reference laboratory. The preparation procedure will involve taking a blood sample in a 5-mL tube containing no anticoagulants. This sample will be centrifuged in a standard bench-top centrifuge for 15 minutes at 3000 rpm, and the resulting serum separated from the cells and stored at –20°C before shipment to the central laboratory. A random fecal sample will be collected and stored at –20°C before shipment. The samples will be shipped on dry ice to the reference laboratory, where the serum samples will be analyzed for FGF-19 by enzyme-linked immunosorbent assay (ELISA), and for C4 and fractionated bile acids by liquid chromatography–mass spectrometry (LC-MS) using established techniques.

The SeHCAT test will be performed in the Nuclear Medicine Department of each participating center, following a standard protocol, under the supervision of an Administration of Radioactive Substances Advisory Committee (ARSAC) certificate holder [13]. A capsule containing radiolabeled SeHCAT will be administered to the patient orally according to a standard procedure and considering manufacturer’s recommendations. Patients will receive specific instructions regarding their food intake. After 3 hours, a scan will be performed to measure the baseline SeHCAT activity.

The patient will be requested to return to the Nuclear Medicine Department on day 7 to undergo a second scan to measure the retention of SeHCAT, thus completing the test. The SeHCAT test result will be concealed from the clinician and the patient until the 2-week follow-up appointment. On the visit to complete the SeHCAT test, BAS will be dispensed to allow the patient to commence treatment on the following day. BAS will be prescribed to all patients according to a standard protocol based on current clinical practice.

All patients will attend a follow-up appointment with the gastroenterologist 2 weeks after the initiation of treatment with BAS. A clinical assessment will be performed to capture the relevant outcome measures: the patient’s adherence to treatment, improvement of symptoms, and quality of life (QoL). The QoL assessment will be undertaken by a research nurse trained in qualitative methodology. The clinical assessment will determine whether there has been a positive or negative response to BAS treatment. A standardized definition will be agreed for the degree of improvement in symptoms required to represent a positive response to treatment. At the follow-up appointment, the SeHCAT test result will be revealed to the clinician and the patient. A positive response to treatment at 2 weeks with evidence of treatment adherence will be used as the gold standard that defines a diagnosis of BAM.

Patients with a negative response to treatment will stop BAS treatment promptly (irrespective of SeHCAT test result) and may be directed to other investigations. At this stage, blood and fecal samples will be collected from this group for assessment of biomarkers. Patients with a positive response to BAS treatment (irrespective of SeHCAT test result) will continue on BAS treatment for a further 2 weeks. For this group, a second follow-up appointment will be performed at 4 weeks to repeat the outcome assessment. At this second follow-up visit, blood and fecal samples will be collected for further biomarker testing.

At 8 weeks, all patients entered into the study will be contacted for a telephone follow-up appointment to collect final follow-up data. Any interventions other than those included in the study protocol will be recorded during the study period.

**Figure 1 figure1:**
[figure not shown]
Study procedure.

### Data Collection

Relevant clinical data regarding the care pathway, diagnostic tests, and interventions will be collected using electronic case report forms. Patient follow-up data will be collected using a questionnaire to be developed according to the Diagnostic Criteria for Functional Gastrointestinal Disorders (“the Rome criteria”) [14]. Quality of life measures will be captured using the standard EQ-5D tool [15].

All study data will be entered onto a database by qualified research staff and subjected to quality control checks. Patient-identifying details will not be included in any study data electronic files. After the closure of the study, the participating sites will maintain all source documents, study-related documents, and copies of the paper source documentation forms, data query, and amendment forms in compliance with local center policies. All source documents will be retained for a period of 10 years following the end of the study.

### Sample Size

Sample size was calculated based on the 95% confidence intervals of the sensitivity and specificity of the SeHCAT test result in predicting true BAM as defined by response to BAS treatment [16]. The prevalence of BAM in this population of patients attending gastroenterology appointments with chronic diarrhea is estimated to be approximately 50% [6]. Assuming a minimum value of 70% for either sensitivity or specificity [7], a sample of 600 patients (and therefore 300 true positives) would give an acceptable 95% confidence interval of 65% to 75%. Sensitivities or specificities closer to 1 will have narrower confidence intervals. If the assumption of 50% true positives is incorrect, an alternative scenario of 3:1 positives to negatives would give a 95% confidence interval of 62% to 77% around a specificity of 70%.

### Statistical Analysis

Results of the SeHCAT test (percentage retention per patient) will be presented using suitable descriptive methods, including frequencies, proportions, means, and standard deviations, as appropriate. Response to BAS treatment will be presented as a proportion of those who initiated the treatment. All descriptive statistics will be presented with 95% confidence intervals.

The diagnostic accuracy of the SeHCAT test to provide a positive indication of BAM compared with the gold standard of a positive response to BAS at 2 weeks of treatment adherence will be investigated using the receiver operating characteristic (ROC) curves approach to compare different choice of thresholds. Sensitivity, specificity, positive predictive value, negative predictive value, likelihood ratios, and area under the curve will be calculated and presented with 95% confidence intervals. Multivariable logistic regression models will be used to assess the association between presence of BAM and continuous SeHCAT retention levels after adjustment for confounders.

Similar methods will be used to assess the diagnostic accuracy of biomarkers in the prediction of BAM. The diagnostic accuracy of the selected biomarkers will be compared to that of the SeHCAT test using the McNemar test for paired proportions.

Where diagnosis of BAM is confirmed, the association between severity of BAM (as assessed clinically at baseline) and the continuous SeHCAT result will be investigated using appropriate multivariable regression models taking into account prognostic baseline variables as potential confounders.

The EQ-5D scores [15] will be derived using standard procedures and will be used to describe the QoL of different subgroups. The change in QoL for the SeHCAT-positive group who respond positively or negatively to BAS will be examined and compared using regression methods adjusting for prognostic variables including QoL at baseline.

All analyses will be 2-sided with 5% significance level and will be reported according to the international standards for the reporting of diagnostic accuracy studies [17].

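### No SeHCAT cut-off is fixed in advance, so accuracy reported at cut-offs derived from the same 600 patients will be somewhat optimistic, most of all in the small Type 1 group

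*Protocol article*

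**What the plan says.** Under Objectives, the primary aim is the diagnostic accuracy of SeHCAT against response to a bile acid sequestrant. The research questions ask for the optimal cut-offs, ask whether separate ones can be set for each clinical population, and then ask "How do the cut-off thresholds currently in use for SeHCAT in UK centers compare with these optimal values".

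Statistical Analysis answers this in one sentence: accuracy "will be investigated using the receiver operating characteristic (ROC) curves approach to compare different choice of thresholds". Sensitivity, specificity, predictive values, likelihood ratios and area under the curve (AUC) follow, each with a 95% confidence interval. No primary cut-off is named.

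Sample Size states: "Sample size was calculated based on the 95% confidence intervals of the sensitivity and specificity of the SeHCAT test result". It proceeds "Assuming a minimum value of 70% for either sensitivity or specificity" and attaches no cut-off to that value.

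The Introduction supplies candidates. Among UK definitions of an abnormal result it lists "a single threshold value (of which <15% retention was the most common"), and it mentions 8% retention from two earlier treatment-response studies. Neither is adopted in Methods.

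**The concern.** Sensitivity and specificity exist only at a stated cut-off. If that cut-off is the one that looks best in the study data, the search also picks up chance features of those data, and the same patients then return accuracy that is too high. The effect grows as the group shrinks, and the protocol raises population-specific cut-offs although Type 1 was only 14% of the earlier survey.

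Two uses of the results are at stake:

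- **Reported accuracy.** The figures quoted for any new cut-off would be slightly too favourable overall and clearly too favourable in a small population.
- **Comparison with current practice.** If derived and current cut-offs are set against each other on accuracy in the same sample, the direction of the result on the selecting criterion is known beforehand.

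**Working it through.** **1. The plan's own intervals.** Inputs from Sample Size: 600 patients, prevalence about 50% (so 300 per group), and sensitivity or specificity 70%.

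- Wald interval for 210/300: 0.70 ± 1.96 × √(0.70 × 0.30 / 300) = 0.70 ± 0.052, or 64.8% to 75.2%. The Wilson interval is 64.6% to 74.9%. The plan states 65% to 75%.
- 3:1 scenario, 150 negatives, 105/150: Wald 62.7% to 77.3%, Wilson 62.2% to 76.8%. The plan states 62% to 77%.

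Both stated intervals reproduce (Wilson rounds to each), so the arithmetic is sound. They describe a proportion at a cut-off fixed before the data are seen.

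**2. Optimism when the cut-off is chosen on the same data.** The protocol gives neither a score distribution nor a selection criterion, so these are assumptions:

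- Scores are normal with equal variance, separated by d = 2 × z(0.70) = 1.049. The best cut-off then truly has 70% sensitivity and 70% specificity, and AUC is 0.77.
- The cut-off maximises the Youden index J = sensitivity + specificity − 1.
- Optimism is apparent J at the chosen cut-off minus true J at that cut-off, averaged over 4,000 simulated studies.

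Group sizes: Type 1 is 0.14 × 600 = 84. The rest was split fairly equally between Types 2 and 3, so (600 − 84) / 2 = 258 each. Splits within groups are assumed.

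| Responders / non-responders | Apparent J | True J at chosen cut-off | Optimism (points) | Sensitivity | Specificity |
|---|---|---|---|---|---|
| 300 / 300 | 0.423 | 0.393 | 3.0 | 1.6 | 1.4 |
| 450 / 150 (the plan's 3:1 case) | 0.426 | 0.392 | 3.4 | 1.0 | 2.4 |
| 129 / 129 (Type 2 or 3) | 0.437 | 0.389 | 4.9 | 2.6 | 2.3 |
| 42 / 42 (Type 1) | 0.468 | 0.378 | 9.0 | 5.1 | 3.9 |

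For a Type 1 group of 84 split 63/21 or 71/13, total optimism is about 11 or 14 points, most of it on the smaller group's measure. With a truth of 80% and 80%, it is 2.3 points at 300/300 and 7.6 at 42/42.

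**3. Coverage at 300/300.** A nominal 95% interval at the chosen cut-off covers the true sensitivity there in about 89% (Wald) to 92% (exact) of studies. For specificity the figures are about 91% and 93.5%.

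**4. Derived against current cut-off.** For any fixed cut-off c₀, the maximum of J(c) over all c in the sample is at least J(c₀) in that sample. So the derived cut-off can tie or win but not lose. When c₀ was set to the true optimum at 300/300, the derived cut-off looked better in 98% of studies, by 2.2 points of sensitivity plus specificity on average, and worse in none.

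**The case against.** The article condenses a fuller plan. The selection criterion, the interval method and any internal validation may properly sit in an analysis plan that is not shown. Finding the threshold is itself a research question, so fixing one in advance could seem to miss the purpose. The question about current cut-offs can be read as comparing retention values, say 15% against a derived figure, and nothing then favours the derived value by construction. Future Directions says that the results need validation elsewhere.

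Much of this stands. Absent internal validation is not in itself a fault of the article, and the comparison of values is unaffected. Also untouched are AUC, the logistic model on continuous retention, accuracy at any established cut-off, and the tertiary biomarker comparison, which is restricted to established cut-offs.

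What remains is that the protocol's primary accuracy aim and its sample size use a sensitivity and specificity that are undefined until a cut-off is named. Later validation in other populations does not correct the estimates published from this study.

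Two stronger readings are tempting and not supported:

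- A reader might infer that the study is bound to declare its new cut-off better than current practice. No test of derived against current cut-offs is planned, and the wording does not say that they are to be compared on accuracy.
- A reader might infer that the stated precision collapses, because sensitivity at a selected cut-off varies across simulated studies with a standard deviation of 6.9 points against a binomial standard error of 2.6. Nearly all of that is real movement of the operating point along the ROC curve. The standard deviation of estimate minus truth is about 2.5 points, close to the binomial value.

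**Conclusion.** The point holds in limited form. In the full sample the bias is modest: about 1.5 points per measure against an interval half-width of about 5, with coverage a few points below nominal. The interval of 65% to 75% is correct for a cut-off fixed in advance and slightly too optimistic for one chosen from the data. In a Type 1 group of about 84 the bias is material: about 5 and 4 points with an even split, and more if responders and non-responders are unbalanced.

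The one-sided comparison arises only if current and derived cut-offs are judged on in-sample accuracy.

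The sizes depend on the assumed normal scores, Youden selection and group splits, and on the overall discrimination also applying within Type 1. The survey's median retention of 2% in Type 1, against 17% to 18% in the other types, makes that last assumption uncertain. The direction of the bias at a selected optimum does not depend on these choices. The change should be made before the study starts.

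**What to change.** In Sample Size and Statistical Analysis:

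- Name one established cut-off in advance for the primary sensitivity and specificity estimates, and state that the planned precision refers to it. Retention below 15% is an obvious candidate because the Introduction reports it as the most common single threshold, with 8% shown alongside. Any established value would serve; this is an analysis threshold, not advice on clinical use.
- Label derived and population-specific cut-offs exploratory, and state the selection criterion.
- Report sensitivity and specificity at derived cut-offs with a bootstrap optimism correction that re-selects the cut-off in each resample, and give a confidence interval for the cut-off itself.
- Make any accuracy comparison of current and derived cut-offs on the corrected values.

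No patients, visits or samples are added. The cost is wording, a bootstrap, and slightly less favourable figures for derived cut-offs. Funding is still being sought, so the change is cheap now.

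### Whether SeHCAT accurately grades BAM severity is to be answered only by an adjusted association with baseline severity, which does not measure grading accuracy

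*Protocol article*

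**What the plan says.** Two statements under Objectives concern severity. A secondary objective is "The feasibility of using the SeHCAT test to provide an indication of the severity of BAM (eg, mild, moderate, or severe" (the quotation stops before the closing bracket). The matching research question is stronger: "Is SeHCAT an accurate test to grade the severity of BAM".

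The Statistical Analysis section gives one analysis for both. It opens "Where diagnosis of BAM is confirmed", so it is limited to patients who meet the reference standard. It continues that "the association between severity of BAM (as assessed clinically at baseline) and the continuous SeHCAT result will be investigated". The method named is multivariable regression, with adjustment for baseline prognostic factors.

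For the presence of BAM the same section plans ROC curves, sensitivity, specificity, predictive values, likelihood ratios and AUC with 95% confidence intervals, and adds a logistic regression for association. For severity it names no accuracy, agreement or concordance measure and no retention bands.

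**The concern.** A question about accurate grading needs an analysis that compares the grade implied by the test with the grade on the reference scale. An adjusted regression coefficient answers a different question: whether retention is related to severity once other predictors are held fixed. Two features separate it from grading accuracy. Its significance depends on sample size as well as on strength of relationship, so a weak relationship can be clearly significant. Its adjustment also moves the estimate away from what the test achieves on its own, which is what a clinician reading a retention value would use.

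The practical stake is stated in the Introduction, which reports that some UK centers already divide results into three categories or into four (normal, mild, moderate, severe). If the severity analysis is carried out as written, the study will end without an estimate of how well any such division matches clinical severity.

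**Working it through.** **Inputs from the article.** The sample is "a sample of 600 patients (and therefore 300 true positives", and prevalence "is estimated to be approximately 50" percent (both Sample Size): 600 × 0.50 = 300 with confirmed BAM. Tests are two-sided at 5% (Statistical Analysis).

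**The plan's own figure.** No power or precision is given for the severity analysis. The stated interval for 70% sensitivity with 300 patients is 65% to 75%. The Wilson interval is 64.6% to 74.9%, so it reproduces. The size of 300 is used below.

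**Step 1: smallest significant correlation.** A simple correlation stands in for the planned adjusted coefficient. The critical value is |r| = t/√(n − 2 + t²). With n = 300 and t = 1.968 on 298 degrees of freedom, |r| = 1.968/√(298 + 3.873) = 0.113. If 450 patients had BAM (the 3:1 scenario under Sample Size), it would be 0.092; with 150 it would be 0.160.

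**Step 2: power.** By Fisher's z, power ≈ Φ(√(n − 3) × atanh(r) − 1.96), with √297 = 17.23. For r = 0.20: 17.23 × 0.2027 − 1.96 = 1.53, so power is 94%.

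**Step 3: grading at those correlations.** This step needs assumptions that are not in the article: bivariate-normal severity and retention, with retention oriented so that lower values mean worse disease, and the same grade shares on both scales. Results are from 2,000,000 simulated pairs per row, with equal thirds (33.3% agreement by chance).

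| True r | Power, n = 300 | Correct grade | Linear-weighted kappa | AUC, severe vs rest |
|---|---|---|---|---|
| 0.113 | 50% | 36.4% | 0.07 | 0.55 |
| 0.161 | 80% | 37.8% | 0.10 | 0.57 |
| 0.20 | 94% | 38.9% | 0.12 | 0.59 |
| 0.30 | >99.9% | 42.1% | 0.19 | 0.64 |
| 0.50 | >99.9% | 49.2% | 0.32 | 0.74 |

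With grade shares of 50:30:20, agreement by chance is 38.0%. At r = 0.20 agreement is 43.3%, weighted kappa 0.12 and AUC 0.60, so the reading does not depend on equal thirds.

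**Step 4: can grading be estimated at this size?** For a correct-grade proportion of 38.9% in 300 patients, the 95% half-width is 1.96 × √(0.389 × 0.611/300) = 5.5 points. That is close to the 5-point half-width that the article calls acceptable for sensitivity.

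**The case against.** The formal secondary objective speaks of feasibility and of an indication of severity, and for that wording an association is a reasonable first step. The article is also condensed: a fuller plan could use an ordinal model and report concordance. Both points carry weight and keep this from being a major finding. They do not remove it. The research question asks about accuracy, and the article specifies accuracy measures for presence of BAM while choosing association for severity. An analysis plan that followed the text faithfully would still leave the question unanswered.

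Three stronger readings are tempting, and the article does not support them.

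- A reader might infer that the planned regression is almost certain to be positive. No correlation between retention and severity is given. At n = 300, power is 41% at r = 0.10 and 74% at r = 0.15; near-certainty appears only if a larger r is chosen. The 300 also assumes no loss or non-adherence, and the calculation is for an unadjusted correlation.
- A reader might infer that baseline clinical severity is the wrong yardstick and that symptom change on BAS should be graded in all treated patients. The Introduction does say "Studies have found a relationship between SeHCAT retention levels and response to BAS treatment, with lower retention levels associated with greater resolution of symptoms", but that does not make response a measure of severity. The Challenges section warns that BAS may not always work in BAM and that improvement may be a placebo response. Response also defines the diagnosis, and non-responders are coded as not having BAM, so grading BAM severity in them would be incoherent.
- A reader might infer that the study intends to endorse mild, moderate and severe reporting from a significant coefficient. No section says so.

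The grading figures are open to the objection that retention may be skewed or mixed: the Introduction cites survey medians of 2% for Type 1 and 18% and 17% for Types 2 and 3. They are therefore illustrations and not predictions.

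**Conclusion.** The point holds as a mismatch between question and analysis. The one severity analysis in the article can establish a relationship but cannot show whether SeHCAT grades severity accurately. The size of the gap, under the stated assumptions, is that a correlation detected with 94% power (r = 0.20) corresponds to about 39% correct grades against 33% by chance, and significance can occur from about |r| = 0.11. The 300 patients and the 5% level are the article's own; the normal scales and grade shares are assumed; the true correlation is unknown and could be strong enough for useful grading. The planned analysis would not tell the two situations apart. The primary accuracy analysis is unaffected, and the point should be corrected before the study starts.

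**What to change.** In Statistical Analysis, keep the adjusted regression as supportive and add the following in confirmed BAM, all with 95% confidence intervals:

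1. An unadjusted ordinal concordance index of retention against the baseline clinical severity grade, or the AUC for severe versus the rest.
2. A cross-classification of pre-specified retention bands against that grade, with correct-grade proportions and weighted kappa. The Introduction mentions three- and four-category schemes but gives no limits for them, so the study team must fix the bands in advance.
3. A sentence stating that association alone will not be read as evidence of grading accuracy.

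If the team does not want a grading analysis, reword the research question to ask whether retention is associated with clinical severity.

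The additions use the retention values and the baseline clinical severity assessment that the regression already needs, provided that severity is recorded as a grade. The cost is protocol wording and a few tables. The downside is that the severity conclusion may be less favorable than a significant coefficient would suggest.
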